# SYNOPSIS

| **Study Title** | Trial of Exercise to Prevent Hypertension in young Adults | |
| --- | --- | --- |
| **Internal ref. no. / short title** | TEPHRA | |
| **Study Design** | Randomised Control Trial | |
| **Study Participants** | Young adults aged 18 to 35 years old with preterm birth (less than 37 weeks gestation) and full term birth (37 or more weeks gestation) histories, clinic systolic blood pressure of between 110 and 159 mmHg or diastolic pressure blood pressure between 70 and 99 mmHg and/or 24 hour awake ambulatory systolic blood pressure between 115 and 151 mmHg or diastolic pressure blood pressure between 75 and 96 mmHg. | |
| **Planned Sample Size** | 220 participants (100 preterm and 100 full term; 20 healthy participants) | |
| **Planned Study Period** | January 2016 to 31^st^ May 2021 | |
|  | **Objectives** | **Outcome Measures** |
| **Primary** |  |  |
|  | To compare the effect of physical activity and aerobic exercise intervention versus usual care/minimal intervention on awake blood pressure levels in young adults of varying gestational age with elevated blood pressure | Systolic and Diastolic blood pressure measured during 24 hour ambulatory blood pressure at baseline and upon completion of 16 week intervention |
| **Secondary** |  |  |
|  | To compare the sustained effect of physical activity and aerobic exercise intervention versus usual care/minimal intervention on awake blood pressure levels in young adults of varying gestational age with elevated blood pressure | Systolic and Diastolic blood pressure measured during 24hour ambulatory blood pressure at baseline, upon completion of 16 week intervention, and at and 52 weeks post-baseline |
|  | To compare the effect of physical activity and aerobic exercise intervention versus usual care/minimal intervention on cardiopulmonary exercise performance in young adults of varying gestational age with elevated blood pressure | Oxygen uptake and carbon dioxide exchange kinetics across submaximal and peak exercise |
|  | To compare the effect of physical activity and aerobic exercise intervention versus usual care/minimal intervention on central blood pressures and vascular stiffness in young adults of varying gestational age with elevated blood pressure | - Pulse wave velocity - Augmentation index - Central blood pressure |
|  | To investigate cardiac adaptation and remodelling following exercise intervention in preterm and full term born participants compared to non-exercising controls | Cardiac Echocardiography (all participants n=200)  -Cardiac Mass  -Ventricular Structure and Function  -3D-shape and functional analysis  Cardiac MRI (N=100)  -Cardiac Mass  -Ventricular Structure and Function  -3D-shape and functional analysis |
|  | To investigate the change in microvascular structure and function post exercise intervention compared to control | Retinal Imaging  Dermal Capillaroscopy |
|  | To access the degree of natural variability of circulating angiogenic and vascular biomarkers in the blood of healthy volunteers | Blood analysis tests including but not limited to protein and gene-expression assays |
|  | To quantify mean changes in circulating angiogenic and vascular markers and biomarkers at rest and following peak exercise between intervention and control participants | Whole, plasma, and serum blood samples at rest and following peak exercise testing |
|  | To investigate levels of vasoactive markers and biomarkers related to renal function at rest and following peak exercise between intervention and control participants | Whole, plasma, and serum blood samples at rest and following peak exercise testing |
|  | To investigate neurophysiological remodelling following exercise intervention compared to control | Brain MRI (N=100)  -Ventricular volume and shape  -Presence of white matter lesions  -White matter microstructural differences including fractional anisotropy  -Vessel Density and Tortuosity  Gait analysis accelerometry profile |
|  | To investigate hepatic remodelling and mean change in hepatic adiposity pre and post exercise intervention compared to control | Liver MRI (N=100)  Liver MRI Endpoints  Structure and volume  Intra-hepatic lipid content  Steatohepatitis  Hepatic fibrosis |
|  | To investigate the correlation between physical activity behaviour change and participants’ cognitive and psycho-social determinants of exercise including self-efficacy to exercise and motivations to exercise | Objective measure of physical activity (7 day wear of activity monitor)  Self-reported questionnaire responses, including self-reported physical activity questionnaires, cognitive and psycho-social questionnaire items and self-efficacy measures. |
| **Tertiary** |  |  |
|  | Participant experience: assessment of individual experience following intervention | Structured interview (participants) |
|  | Economic evaluation: assessment of feasibility for scaling intervention to multi-centre trial including intervention process evaluation | EQ-5D-5L health questionnaire results  Structured interviews (study team and personnel)  Review of medical notes/GP consultations |

# ABBREVIATIONS

| AE | Adverse Event |
| --- | --- |
| CI | Chief Investigator |
| CRF | Case Report Form |
| CTRG | Clinical Trials & Research Governance, University of Oxford |
| GCP | Good Clinical Practice |
| GP | General Practitioner |
| ICF | Informed Consent Form |
| NHS | National Health Service |
| PI | Principal Investigator |
| PIL | Participant/Patient Information Leaflet |
| R&D | NHS Trust R&D Department |
| RCT | Randomised Control Trial |
| REC | Research Ethics Committee |
| SOP | Standard Operating Procedure |

# BACKGROUND AND RATIONALE

**Early Hypertension**

Hypertension contributes to 9 million annual global deaths^1^. In the United Kingdom, 1 in 4 adults over the age of 25 are hypertensive and the incidence in the 18 to 40 year old population may be increasing^2^. North American population studies report incidence as high as 1 in 5 of the under-40 age group^3^. Targeted early treatment and primary prevention may have significant benefits on future morbidity and mortality. Blood pressure reductions of as little as 2 mmHg may be enough to reduce future stroke risk by 10%^4^. To drive improvement in primary prevention strategies more understanding is required of the effectiveness of lifestyle and behavioural intervention to lower blood pressure in adults with early cardiovascular risk. This includes investigation of the response to intervention in young adults known to have unique cardiovascular phenotypes associated with early life exposures and familial risk. Prevalence of hypertension is higher in young adults with history of preterm birth and exposure to maternal pregnancy complications such as pre-eclampsia^5–8^. Our recent work supports distinct aetiological pathways for this early cardiovascular risk^9^. The differences observed in blood pressure between preterm and full term born groups track from childhood and by early adulthood approach 10mmHg difference in systolic blood pressure, resulting in a 2-3 fold increase risk of early hypertension.^6,10,11^ In the UK 6-12% of the population are born preterm equivalent to 1-2 million young people at risk of early hypertension. This predicted cardiovascular risk burden is supported by our recent analysis of the Raine Western Australia longitudinal birth cohort, which identified that 1 in 3 adults diagnosed with hypertension before the age of 30 had been exposed to pregnancy complications^12^.

**Trial Rationale**

Physical activity promotion may be an attractive and acceptable strategy to improve cardiovascular health in young adults at risk of early hypertension and cardiovascular disease^13^. Our recent systematic review of exercise interventions demonstrated reductions of up to 5mmHg in systolic and diastolic blood pressure following supervised exercise. However, the review identified significant deficiencies in the investigation of exercise response in adults under 40 years of age. In addition, there is limited explanation of heterogeneity in blood pressure response following exercise training in the general population or across subgroups. Due to the unique cardiovascular phenotype of those born premature, it is uncertain whether, as adults, they will have the same blood pressure response and beneficial cardiovascular adaptation as observed in the wider population. The proposed randomised control trial will investigate the effects of exercise intervention on a young adult population with pre-hypertension or stage 1 hypertension. The trial includes a subgroup of participants born preterm and compares them to a control group born full term.

**Predicted cardiovascular exercise adaptations and support for proposed outcome measures**

- **Blood Pressure**

Our recent systematic review of RCTs delivering exercise interventions in young adults with prehypertension or stage 1 hypertension reported mean decrease of 5.4 mmHg and 5.43 mmHg in systolic and diastolic blood pressures following 3 to 6 months of supervised intervention. The proposed trial will be powered to achieve similar post interventions effects in blood pressure, reporting 24 hour ambulatory blood pressure as the primary outcome at 16 and secondarily at 52 weeks. 24 hour ambulatory blood pressure monitoring is the gold standard measure used in diagnosis and management of high blood pressure.

Our pilot data supports cardiovascular fitness as a mediator of lower blood pressure in adults with history of preterm birth or exposure to pregnancy complication. Systolic and diastolic blood pressures were 5mmHg and 10mmHg lower in preterm born adults with higher cardiovascular fitness, which we reported as exercise capacity above 30 ml/kg/min. The distinctions in blood pressure associated with fitness were more marked in preterm compared to full term born groups when applying the same criteria. This supports the hypothesis that adults with preterm birth and pregnancy complication may have lower resilience to the risks of sedentary behaviour and lower cardiovascular fitness.

- **Cardiac Structure and Function**

We have previously used 3-dimensional mesh analysis of cardiovascular magnetic resonance images to demonstrate prematurity is associated with significantly increased cardiac mass, shortened ventricles and reduced cavity size compared to adults born at term^14,15^. These features are associated with impaired systolic and diastolic myocardial deformation and 20% of the preterm cohort had right ventricular (RV) ejection fractions below the lower limit of the control group, with 6% fulfilling clinical criteria for RV dysfunction^14,15^. Cardiovascular adaptation following exercise training may lead to significant improvement across these parameters^13,16,17^. To meet increasing metabolic demand, cardiac output increases in response to exercise. This is associated with remodelling of the atria, ventricular walls and respective cavity sizes leading to increased end diastolic volumes and improved myocardial function. It is currently unknown whether these anticipated changes will be demonstrated in the preterm cardiovascular phenotype. To track potential changes in cardiac structure and function, study participants will undergo detailed cardiac ultrasound imaging and a subgroup of participants will complete detailed MRI imaging.

- **Microvascular Function and Angiogenesis**

We have observed a significantly altered circulating anti-angiogenic profile in adults born preterm, including elevations in soluble endoglin (5.64± 1.03 vs 4.06±0.85 ng/mL) and soluble fms-like tyrosine kinsase-1 (88.1±19.0 vs 73.0±15.3 pg/mL)^14^. Furthermore, these elevations are associated with reductions in capillary density (r=-0.57, p=0.002), which, in mediation analysis, accounted for increases in 24-hour systolic blood pressure (r=-0.55, p=0.01). Changes in peripheral capillary density and peripheral resistance are known to be an early adaptation to exercise^18,19^. Exercise-induced angiogenesis may be a key factor influencing cardiovascular adaptation and altering the risk profile of preterm born adults^20^. Angiogenic adaptation in response to exercise will be compared across the subgroups defined by gestational age. Angiogenic and vascular function markers and biomarkers will be measured from blood samples at baseline and follow-up, pre and post exercise testing and will be correlated with resting microvascular measures such as dermal capillaroscopy and retinal imaging.

- **Vasoactive Renal Function Analysis**

Renal function exerts a potent influence on blood pressure and vascular function through multiple mechanisms including moderating the Renin Angiotensin Aldosterone System (RAAS). Pharmaceutical blockade of angiotensin II and its pressor effect is an established and effective practice in clinical treatment of hypertension^21^. A recent systematic review linked exercise to reductions in angiotensin II levels^22^, though other research has suggested that angiotensin II levels may not be significantly altered by exercise^23^. Other research suggests that pre-eclampsia is associated with increased angiotensin II sensitivity^24^. However, angiotensin (1-7) appears to oppose some effects of angiotensin II and is associated with reduced blood pressure when orally administered to Spontaneously Hypertensive Rats^25^. In humans, reduced levels of angiotensin (1-7) have been linked to preterm birth^26^. Preliminary research also indicates that biomarkers may be able to play a role in characterizing RAAS function and activation^27^.

Characterizing markers and biomarkers related to RAAS activity may help to better understand the aetiology of hypertension in the trial groups and how this pathway is affected by chronic aerobic exercise.

**Neurophysiological adaptation**

Elevated blood pressure is a major risk factor for future cerebrovascular incidents^4^ and may be a more significant risk factor for preterm born adults and those exposed to pre-eclamptic pregnancy. Strikingly, the risk of stroke before the age of 50 years in adults exposed to pregnancy complications is increased 2-3 fold.^28^ Potential explanation for increased stroke and hypertensive risk is the unique pathophysiological vascular development during the perinatal period. Cerebral magnetic resonance (MR) angiography in neonates born preterm has demonstrated a significant developmental immaturity including reduced tortuosity in cerebral arteries, as well as sparser and less complex peripheral vessels^29^. Vascular density in the white matter has been shown to remain low compared with other brain regions^30^ and these differences may, in part, underlie reports of poor cerebral perfusion in the pre-term neonatal brain^31^. The observed differences in perfusion have been associated with regional hypoxia-ischaemia, particularly in the white matter, which is likely to ultimately predispose to white matter injury. The cerebral and retinal microvasculature share similar characteristics^32^, and clinically visible retinopathy signs are associated with an increased risk of stroke^33^. Subjects with early structural changes in retinal microvasculature are more likely to have cerebral microbleeds^34^, suggesting changes in retinal vascular health may reflect cerebrovascular health.

Physical activity is associated with a decreased stroke incidence^35,36^ and animal studies investigating brain damage after induced stroke show marked decreases in neuronal damage, infarct volume and improved survival in animals undergoing exercise preconditioning^37,38^. Exercise-induced angiogenesis may be a key factor in this response. An MR angiography study in older adults revealed a greater number of small vessels in the brains of aerobically active individuals compared with those less active^39^, and animal studies have repeatedly reported cerebral angiogenesis in response to physical exercise ^40,41^. Rats undergoing exercise preconditioning show a 10-fold increase in microvessel density in the striatum compared with controls, coupled with significantly reduced infarct volume and neurological deficits following induced stroke^38^. To track potential cerebral vascular adaptations to exercise, all participants will have retinal microvascular measures and a subgroup will have detailed cerebrovascular brain imaging. Our collaborators have been able to demonstrate optimal adaptation in the retinal microvascular in obese pre-hypertensive adults following exercise training^42^. The use of detailed MR angiography will allow for tracking of similar changes across the cerebral vascular beds.

**Exercise and Metabolic Health**

Risk of metabolic dysfunction is well established in preterm cohorts^11^ and highly correlated with cardiovascular risk in the general population. Hepatic structure and function may be a primary determinant of metabolic status^43^. A primary driver of optimal hepatic structure and function is believed to be cardiovascular fitness^44–46^. Improved cardiovascular fitness and reductions in fatty liver content are closely associated^46^. Further investigation is required to clarify if cardiovascular risk reduction and positive exercise training adaptation in young adult populations with pre-hypertension are correlated with hepatic structure and function. Detailed liver MRI will be completed on the subgroup of participants undergoing MRI imaging at baseline and follow-up.

**The purpose of the TEPHRA blood cell and biomarker validation sub-study**

Hypertension affects 1 in 4 adults in the UK and increases the risk of cardiovascular diseases and stroke. It is caused by a multitude of factors. As part of an ongoing trial, TEPHRA study is a randomised controlled trial to determine whether modification of lifestyle through an exercise intervention can reduce heart and blood vessel risk in young adults. In the sub-study, healthy participants will undergo measurements of specific characteristics of blood cells and circulating factors in venous blood obtained from veins as part of protocol validation. It is crucial to validate how blood cells and circulating factors vary naturally from day to day in the same individual.

# OBJECTIVES AND OUTCOME MEASURES

| **Objectives** | **Outcome Measures** | **Time-point(s) of evaluation of this outcome measure (if applicable)** |
| --- | --- | --- |
| **Primary Objective** |  |  |
| To compare the effect of physical activity and aerobic exercise intervention versus usual care/minimal intervention on awake blood pressure levels in young adults of varying gestational age with elevated blood pressure | Systolic and Diastolic blood pressure measured during 24 hour ambulatory blood pressure at baseline and upon completion of 16 week intervention | Measured at baseline and upon completion of 16 week intervention |
| **Secondary Objectives** |  |  |
| To compare the sustained effect of physical activity and aerobic exercise intervention versus usual care/minimal intervention on awake blood pressure levels in young adults of varying gestational age with elevated blood pressure | Systolic and Diastolic blood pressure measured during 24 hour ambulatory blood pressure at baseline, upon completion of 16 week intervention, and at and 52 weeks post-baseline | Measured at:  - baseline  - upon completion of 16 week intervention  - 52 weeks post randomisation |
| To compare the effect of physical activity and aerobic exercise intervention versus usual care/minimal intervention on cardiopulmonary exercise performance in young adults of varying gestational age with elevated blood pressure | Oxygen uptake and carbon dioxide exchange kinetics across submaximal and peak exercise | Measured at:  - baseline  - upon completion of 16 week intervention  - 52 weeks post randomisation |
| To compare the effect of physical activity and aerobic exercise intervention versus usual care/minimal intervention on central blood pressures and vascular stiffness in young adults of varying gestational age with elevated blood pressure | - Pulse wave velocity - Augmentation index - Central blood pressure | Measured at:  - baseline  - upon completion of 16 week intervention  - 52 weeks post randomisation |
| To investigate cardiac adaptation and remodelling following exercise intervention in preterm and full term born participants compared to non-exercising controls | Cardiac Echocardiography (all participants n=200)   - Cardiac Mass - Ventricular Structure and Function - 3D-shape and functional analysis   Cardiac MRI ( MRI subgroup n=100)   - Cardiac Mass - Ventricular Structure and Function - 3D-shape and functional analysis | Echocardiography completed at:  - baseline  - upon completion of 16 week intervention  - 52 weeks post randomisation (optional)  Cardiac MRI completed at:  - baseline  - upon completion of 16 week intervention |
| To investigate the change in microvascular structure and function post exercise intervention compared to control | Retinal Imaging  Dermal Capillaroscopy | Measured at:  - baseline  - upon completion of 16 week intervention |
| To investigate the degree of natural variability in circulating angiogenic, vascular and vasoactive markers and biomarkers in blood of the healthy volunteers | Blood analysis tests including but not limited to protein and gene-expression assays | Measured at:   - Sub-study baseline visit 1 - Sub-study visit 2 (1 week post visit 1) |
| To quantify mean changes in circulating angiogenic and vascular markers and biomarkers at rest and following peak exercise between intervention and control participants | Whole, plasma, and serum blood samples at rest and following peak exercise testing | Measured at:  - baseline  - upon completion of 16 week intervention  - 52 weeks post randomisation (resting only) |
| To investigate levels of vasoactive markers and biomarkers related to renal function at rest and following peak exercise between intervention and control participants | Whole, plasma, and serum blood samples at rest and following peak exercise testing | Measured at:  - baseline  - upon completion of 16 week intervention  - 52 weeks post randomisation (resting only) |
| To investigate neurophysiological remodelling following exercise intervention compared to control | Brain MRI (MRI subgroup n=100)   - Ventricular volume and shape - Presence of white matter lesions - White matter microstructural differences including fractional anisotropy - Vessel Density and Tortuosity   Gait analysis accelerometry profile | Measured at:  - baseline  - upon completion of 16 week intervention |
| To investigate hepatic remodelling and mean change in hepatic adiposity pre and post exercise intervention compared to control | Liver MRI (MRI sub-group n=100)  Liver MRI Endpoints   - Structure and volume - Intra-hepatic lipid content - Steatohepatitis - Hepatic fibrosis | Measured at:  - baseline  - upon completion of 16 week intervention |
| To investigate the correlation between physical activity behaviour change and participants’ cognitive and psycho-social determinants of exercise including self-efficacy to exercise, motivations to exercise. | Objective measure of physical activity (7 day wear of activity monitor)  Self-reported questionnaire responses, including self-reported physical activity questionnaires, cognitive and psycho-social questionnaire items and self-efficacy measures. | Measured at:  - baseline  - upon completion of 16 week intervention  - 52 weeks post randomisation |
| **Tertiary Objectives** |  |  |
| Participant experience: assessment of individual experience following intervention | Structured interview (participants) | End of trial period |
| Economic evaluation: assessment of feasibility for scaling intervention to multi-centre trial including intervention process evaluation | EQ-5D-5L health questionnaire results  Structured interviews (study team and personnel)  Review of medical notes/GP consultations | End of trial period |

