**4. FIGURES**

eFigure 1. Adjusted mean difference in systolic blood pressure according to level of blood pressure imputed for missing values in the intervention and control arms. From left to right imputed values increase in the intervention arm and reduce in the control arm. Imputed values are based on levels expected in each quantile of the study population. Change is presented as adjusted mean difference in systolic blood pressure after 16 weeks moderate to high intensity exercise in mmHg with 95% confidence interval error bars

[figure not shown]

eFigure 2. Adjusted mean difference in diastolic blood pressure after 16 weeks moderate to high intensity exercise according to level of blood pressure imputed for missing values in the intervention and control arms. From left to right imputed values increase in the intervention arm and reduce in the control arm. Imputed values are based on levels expected in each quantile of the study population. Change is presented as adjusted mean difference in diastolic blood pressure after 16 weeks moderate to high intensity exercise in mmHg with 95% confidence interval error bars

[figure not shown]

eFigure3. Sensitivity analysis using Multiple Imputation by Chained Equations (MICE) on the primary outcomes of 24hour awake ambulatory diastolic and systolic blood pressure. Change is presented as adjusted mean difference in each blood pressure variable between intervention and control groups after 16 weeks moderate to high intensity exercise in mmHg with 95% confidence interval error bars

[figure not shown]

eFigure 4. Forest plots to demonstrate the adjusted mean difference in awake systolic ambulatory blood pressure (Panel A) and awake ambulatory diastolic blood pressure (Panel B) after a 16 week moderate to high intensity exercise intervention compared to a control group according to different subgroups of the study population. Subgroups are based on defined values of baseline body mass index, glucose level, arterial stiffness and left ventricular mass (for those who underwent magnetic resonance imaging) Change is reported as the adjusted mean difference in mmHg with errors bars representing 95% confidence intervals. Abbreviations: BMI = body mass index, LV = left ventricular, SBP = systolic blood pressure, DBP = diastolic blood pressure.

PANEL A. Awake Systolic Ambulatory Blood Pressure

[figure not shown]

PANEL B. Awake Diastolic Ambulatory Blood Pressure

**
[figure not shown]
**

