# STATISTICS AND ANALYSIS

## Description of Statistical Methods

The analysis will be carried out on the basis of intention-to-treat (ITT). This is, after randomisation, participants will be analysed according to their allocated intervention group irrespective of what they actually receive.

Patient demographic characteristics and other baseline information will be summarised by treatment group. Numbers (with percentages) for binary and categorical variables and mean (standard deviation), or median (interquartile or full range) for continuous variables will be presented. Normality of variables will be assessed by visual assessment of the normality curves and the Shapiro-Wilk test. The analysis of the primary outcome will be assessed using analysis of covariance (ANCOVA) adjusting for baseline values and minimisation factors used in the randomisation process. Results will be presented as adjusted mean difference in change in ambulatory blood pressure between randomised groups at 4 months with 95% confidence intervals (CI) and associated two-sided p value. The analysis of secondary outcomes will also be done using analysis of covariance (ANCOVA) to establish a co-variant model to examine the effect of cardiac structure, vascular function and lifestyle behaviours on exercise capacity. Outcomes measured on more than one occasion will be analysed using a mixed effects model. The data collected from the sub-study will be analysed using paired and independent T-test. If the model assumptions are not met and evidence of departure from Normality is observed, transformations of the data will be employed or non-parametric tests will be carried out. Statistical analysis will be carried out using STATA or SPSS statistical software.

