## The Number of Participants

***Primary Outcome 24-hour awake ambulatory blood pressure***

Our systematic review and meta-analysis of randomised control trials identified an average decrease of 5.4mmHg in systolic blood pressure (SBP) post-intervention via supervised exercise in young adults with prehypertension (mean systolic blood pressure at baseline 126 mmHg). The post intervention standard deviation of change was 8.7 mmHg. Our available cross-sectional pilot data suggests that change will be higher in the preterm born participants and participants exposed to maternal hypertension during pregnancy. To calculate the sample size we have been conservative and used an estimated change of 5 mmHg following 4 months of intervention. We have used a SD of 11.3 from the pooled SD for ambulatory systolic blood pressure from our cross-sectional pilot data. To observe a treatment effect on systolic blood pressure of 5mmHg, powered to 80% (p=0.05) requires a total sample size of 164 participants. The SD deviation for the pooled 24 hour awake diastolic blood pressure is 8.3 mmHg. To observe a treatment effect on diastolic blood pressure of 5mmHg, powered to 80% (p=0.05) requires a total sample size of 114 participants. The power calculations for systolic blood pressure are used to determine the final sample size, with adjustment to 200 participants to allow for 18% attrition. To ensure primary objectives for the study are answered the study team may recruit additional participants to replace those who drop out of the study.

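### Systolic and diastolic awake pressure are both primary, each at two-sided 5%, and the protocol gives no rule for success; if either suffices, the family-wise error is about 8–10%.

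*Supplement*

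**What the plan says.** Section 5 of the protocol (and the Synopsis) gives one primary objective, an effect "on awake blood pressure levels in young adults of varying gestational age with elevated blood pressure", and one primary outcome row: "Systolic and Diastolic blood pressure measured during 24 hour ambulatory blood pressure at baseline and upon completion of 16 week intervention". The row holds two pressures and ranks neither.

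Section 11.2, under the heading "Primary Outcome 24-hour awake ambulatory blood pressure", gives a separate calculation for each pressure, both at 80% power and p=0.05: 164 in total for systolic (5 mmHg, SD 11.3) and 114 for diastolic (5 mmHg, SD 8.3). It then says: "The power calculations for systolic blood pressure are used to determine the final sample size". That sentence gives systolic pressure a role in setting N. It does not make it the sole or first test.

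Section 11.1 specifies ANCOVA and a two-sided p value. The result is described as "adjusted mean difference in change in ambulatory blood pressure between randomised groups at 4 months", with no mention of how two such results combine. Section 11.3 promises a detailed statistical analysis plan before the data are received; that plan is not among the documents shown.

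The reported analyses treat both pressures as primary: the caption to eFigure 3 in the supplement speaks of the "primary outcomes of 24hour awake ambulatory diastolic and systolic blood pressure".

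**The concern.** Two primary tests, each run at 5%, give a 5% trial-level error rate only if a rule ties them together: an order, a split of alpha, or a requirement that both succeed. The protocol states none of these. The alpha in Section 11.2 is the full 5% for each pressure, so a reader who lets either pressure carry the claim is following the stated levels and still exceeds 5%.

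The second problem is interpretation. Systolic pressure has the larger SD and the lower power, so even when the intervention works as planned on both pressures, a result with diastolic significant and systolic not is fairly likely. The protocol does not say whether such a trial is positive, negative or inconclusive, which leaves the decision until after the results are known.

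**Working it through.** **Inputs.** From Sections 11.1 and 11.2: difference 5 mmHg for each pressure, SD 11.3 (systolic) and 8.3 (diastolic), alpha 0.05 two-sided, power 80%, attrition 18%. Allocation is 1:1 (Section 8.4). The correlation between the two test statistics is not given in the documents; I take 0 to 0.8 as an assumed range.

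**Step 1: the plan's figure.** Per arm, n = 2σ²(z₀.₉₇₅ + z₀.₈₀)²/δ² = 2 × 11.3² × (1.960 + 0.842)²/5² = 80.2, so 81 per arm and 162 in total. The t-test version gives 82 per arm and 164. With attrition, 164/0.82 = 200. Both stated figures reproduce, which confirms that systolic pressure was sized at an unadjusted two-sided 5%. (The diastolic 114 does not reproduce at 80% power, where 88 to 90 suffice, but it does not set the final N.)

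**Step 2: error rate if either pressure suffices.** With no effect on either pressure, the error is 1 − P(|Z₁| ≤ 1.96 and |Z₂| ≤ 1.96), with (Z₁, Z₂) bivariate normal. At correlation 0 this is 1 − 0.95² = 9.75%.

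| Assumed correlation | Two-sided error | Favourable direction only (nominal 2.5%) |
|---|---|---|
| 0 | 9.75% | 4.9% |
| 0.3 | 9.5% | 4.8% |
| 0.5 | 9.1% | 4.5% |
| 0.7 | 8.3% | 4.2% |
| 0.8 | 7.8% | 3.9% |

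**Step 3: error rate if both are required.** The trial then errs only when both tests reject, which cannot happen more often than one test rejecting alone: at most 5%.

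**Step 4: how often the two pressures disagree.** With 82 per arm and a true 5 mmHg effect on each, the expected z is 5/(11.3 × √(2/82)) = 2.83 for systolic and 5/(8.3 × √(2/82)) = 3.86 for diastolic. Power is Φ(2.83 − 1.96) = 81% and Φ(3.86 − 1.96) = 97%; by t-test the systolic figure is 80%.

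The chance of diastolic significant and systolic not is diastolic power minus joint power:

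- Normal approximation: 97.1% − 78.5% = 18.6% at correlation 0, and 97.1% − 80.7% = 16.4% at 0.8.
- Simulated t-tests: 19.1% at correlation 0 and 16.8% at 0.8.

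So about 17–19%, or roughly one trial in six to one in five. The reverse split (systolic only) is 2.4% or less.

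**Step 5: what each rule costs.**

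| Rule | Family-wise error | Consequence |
|---|---|---|
| Systolic first, then diastolic | 5% | 164/200 kept; systolic power about 80% |
| Both required | at most 5% | 164/200 kept; joint power 79–81% (normal approximation; about one point lower by t-test) |
| Either, at 2.5% each | at most 5% | systolic N rises to 198, and 198/0.82 = 242 recruited; or systolic power is 72% with 164 |

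**The case against.** **The analysis plan is not shown.** Section 11.3 announces one, and the rule for two primary tests is often placed there. This stands to the extent that one can only say that the protocol shown states no rule. It does not remove the point, because the protocol has already fixed the alpha of each primary test and built N on it. A later plan could choose a fixed sequence or a both-must-succeed rule at little cost. It could not split alpha without losing systolic power or adding participants.

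**The protocol joins the two pressures with the word and.** A reader may take that to mean both must succeed, in which case the error is at most 5%. That reading is possible but not stated. It is also why the 8–10% is conditional and must not be read as the trial's actual error rate.

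**The two-sided rate counts significant harm as well as benefit.** True; the favourable-direction column in the working shows the same near-doubling, less marked at high correlation.

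**The reported result is null.** The supplement describes it so, and the adjusted 16-week intervals for both pressures in eTables 2 and 3 include zero. No false-positive claim was made, so the point concerns the plan and not the reported conclusion.

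**A stronger reading.** A reader might infer that the awake mean and the whole-24-hour mean are both open as primary measures, making four contrasts and a still higher error rate. Section 4 omits awake ("reporting 24 hour ambulatory blood pressure as the primary outcome at 16 and secondarily at 52 weeks") and Section 11.1 says only ambulatory. But the Section 5 objective, the heading of Section 11.2, the eligibility criteria in Sections 7.1 to 7.3 and the reported tables all use awake pressure. In the outcome cell, 24 hour is best read as naming the monitor recording. No section plans or reports a test of a separate 24-hour mean as primary. What remains is loose wording, and no error rate for four tests should be attached to it.

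**Conclusion.** The point holds in conditional form. Awake systolic and diastolic pressure at 16 weeks are both primary at two-sided 5%, and the protocol does not say which result or results constitute success. If either suffices, the family-wise error is about 8–10%; the correlation behind that range is assumed. If both are required, there is no inflation. The 17–19% chance of a diastolic-only result does not depend on which rule was intended: it rests on the protocol's own 5 mmHg effect and SDs, 164 evaluable participants, and the same assumed correlation range. This should be corrected; it does not invalidate the sample size.

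**What to change.** In Sections 5, 11.1 and 11.2, and before the data are received, state the success rule:

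- Test awake ambulatory systolic pressure at 16 weeks first, at two-sided 5%. It is the measure that sets the sample size.
- Test awake diastolic pressure at 16 weeks, also at two-sided 5%, only if systolic is significant; otherwise report it as supportive.

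No more participants are needed. What is given up is a confirmatory claim from a diastolic-only effect. If the sponsor prefers to require both pressures, that is also acceptable, and the protocol should then quote the joint power instead of the two separate powers.

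Separately, as a wording correction only, write awake ambulatory pressure in Sections 4 and 11.1 so that they match the Section 5 objective and the Section 11.2 heading.
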